### Questionnaires

Self-reporting scales and questionnaires will be used to assess sleep quality, daytime functioning, and mood. The Pittsburgh Sleep Quality Index (PSQI) (74) is a self-report questionnaire that estimates sleep quality over a 1-month time interval. It includes seven components that assess different aspects of sleep quality, and each of components has a range of 0–3 points. The Global PSQI Score is the sum of the seven component scores, and it has a range of 0–21 points, where “0” reflects no difficulty and “21” reflects severe difficulties in all areas. The Russian version was approved by authors (75) and estimated in the Russian population (76).

The Insomnia Severity Index (ISI) is a brief self-reported tool measuring the perception of the subject of both nocturnal and diurnal symptoms of insomnia (77); the total score ranges from “0” (no symptoms) to “28” (severe symptoms). There is a Ph.D. research made by Rasskazova E.I. that contains a validation of the Russian version of the ISI (78).

The Epworth Sleepiness Scale (ESS) is a questionnaire that measures the subjective degree of sleepiness in common life situations. The patient is told to assess his or her chance to fall asleep in each of eight situations with a 4-point scale. The score of the ESS is the sum of these points; it ranges from 4 to 24 (79). The Russian version of the ESS was approved by the authors (80).

The Visual Analog Scale of Quality of Life (EQ-VAS), the part of EQ-5D, provides information about the health-related quality of life self-assessment of the patient (81). The Russian version of the EQ-5D is validated (82). The visual analog scale has 100 grades, where “100” represents the best imaginable health state, and “0” represents the worst imaginable health state (83). Geriatric Depression Scale (GDS) will be used for mood disorders assessment. It is a 30-item, self-report instrument that uses a “yes/no” format (84). GDS is useful for assessing patients with mild and moderate cognitive impairments, and its score ranges from 0 to 30; a greater score represents a greater risk of depression. The Russian version of the GDS is available and included in the Guidelines for Cognitive Impairment in Older adults approved by the Ministry of Health of the Russian Federation (85).

### Assessment of Cognitive Function

According to the “Diagnostic and Statistical Manual of Mental Disorders, Fifth Edition” (DSM-5), there are six domains of cognitive function: executive function, learning and memory, perceptual motor function, language, complex attention, and social cognition (86). Each domain has subdomains. Executive function consists of working memory, planning, inhibitory control, responding to feedback, flexibility, and decision making. Learning and memory include semantic and autobiographical long-term memory, free and clued recall, recognition memory, and implicit learning. Perceptual motor function is divided into visual perception, visuoconstructional reasoning, and perceptual motor coordination. Language as a cognitive domain includes the ability of grammar and syntax, object naming, fluency, word finding, and receptive language. Complex attention consists of sustained, divided and selective attention, and processing speed. Finally, social cognition includes recognition of emotions and theory of mind. Each domain except social cognition will be evaluated at baseline and after 2 years of follow-up. Both patient groups will receive identical test protocols.

Global cognition including learning and memory visual perception, visuoconstructional reasoning, executive functions, language, and complex attention will be assessed with the validated Russian version of the Montreal Cognitive Assessment (MoCA); the score ranges from 0 to 30 (87, 88). The Russian translation of the MoCA version 7.1 will be used (89).

For evaluation of learning and memory, the 12-word Verbal Memory Test and the Benton Visual Retention Test will be performed. The 12-word verbal memory test measures immediate and delayed recall of verbal material (a list of 12 nouns) using multiple list learning trials with a reminding paradigm (90). The score is the sum of immediate and delayed recall, and it ranges from 0 to 24. The Benton Visual Retention Test measures recall for 10 images with geometric designs; the first two images consist of one major geometric figure, and the other eight images are composed of two major geometric figures and a smaller peripheral figure (91). A multiple-choice administration will be used, when each image is showed for 10 s and then withdrawn; immediately after exposure, the patient is shown a multiple-choice card with four similar images. The subject should choose the identical one to the stimulus design image. The score of the Benton Test is the number of correctly recalled designs, and it ranges from 0 to 10.

The executive function domain will be measured with Frontal Assessment Battery (FAB) (92) ranging from 0 to 18, Trail Making Test (TMT) (93), parts A (the subject should draw a line linking consecutive numbers from 1 to 25) and B (the subject should draw a line linking alternating numbers and letters in sequence). Part B consists of numbers from 1 to 12 and the first 12 letters of the Russian alphabet. The time to complete each part of TMT is recorded, and the examiner will point out errors as they occur. The score is the time in seconds required for performing each part, and A/B ratio that reflects set shifting ability will be also estimated (94). The executive function is also estimated by phonetic verbal fluency test (naming nouns starting with a defined letter in 1 min), which is included in MoCA. The Russian version of the FAB is included in Guidelines for Cognitive Impairment in Older Adults approved by the Ministry of Health of the Russian Federation (85).

Complex attention and processing speed will be measured with the Symbol Digit Modalities Test (SDMT) (95), which is a subtest of the Wechsler Adult Intelligence Scale-Revised (WAIS-R) (96). The score is the correct number of substitutions in 90 s. Only the written response format of the SDMT will be conducted.

Language will be assessed with animal naming against the clock in 1 min (Semantic Verbal Fluency Test) that measures the ability to rapidly generate words from a specified category (97). The score of the task is the number of animals named.

### Neuroimaging

All subjects will undergo brain MRI scanning at baseline as a routine procedure and in the 2-year follow-up as a study procedure. The imaging protocol will include axial T1, T2, T2^*^, fluid attenuated inversion recovery (FLAIR), and diffusion weighted imaging (DWI) scans that will be made on a 3-Tesla scanner (Siemens, Erlangen, Germany). Slice thickness will be 5 mm, with an interslice gap of 1 mm and a matrix size of 192 × 256 pixels.

All the images will be processed with volBrain online software pipeline (98) to make an automated volumetric measurement of WMH. The volume of the white matter lesion will be calculated separately for the periventricular, juxtacortical, infratentorial, and deep white matter areas as well as the total volume of the lesion. Baseline volumes will be subtracted from follow-up volumes to obtain absolute WMH volume change. In addition, proportional volume change will be calculated by dividing the absolute WMH volume change by baseline WMH volume with a percentage display of results.

One trained and blinded rater will evaluate MRI scans with three cross-sectional visual scales [the Fazekas Scale (99), the Scheltens Scale (100), and the cSVD Score (101)] and the Rotterdam progression scale (102). The Fazekas Scale has a range of 0–6. Both in the periventricular and in the subcortical regions, scores 0–3 can be given for absence, mild, moderate, or severe lesions, respectively (99). The Scheltens Rating Scale ranges from 0 to 84: scores 0–6 can be given in 13 subcortical regions (frontal, parietal, temporal and occipital lobes, caudate, putamen, globus pallidus, thalamus, internal capsule, cerebellum, mesencephalon, pons, and medulla) and scores 0–2 for three periventricular regions (frontal caps, occipital caps, and lateral ventricles bands) (100). Change scores will be obtained by subtracting the baseline scores from the follow-up scores. Calculating the total SVD score (range 0–4) will be made by adding up of scores for each cSVD marker: 1 point for presence of any lacunes, 1 point for one or more cerebral microbleeds, 1 point for presence of enlarged perivascular spaces (PVS) in the basal ganglia, and 1 point for presence of moderate to severe PVS in other regions (101). The Rotterdam Progression Scale ranges from −7 to +7, measuring changes in WMH (−1, decrease; 0, no change; and +1, increase) for three periventricular regions (frontal caps, lateral bands, and occipital caps) and four subcortical regions (frontal, parietal, temporal, and occipital) (102).

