On the contrary, the cognitive impairment in cSVD is fully investigated, and it involves similar changes in executive functions, attention, language fluency, and set shifting (58, 59). MRI features of cSVD are summarized in STRIVE criteria (STandards for ReportIng Vascular changes on nEuroimaging). They consist of WMH, recent small subcortical infarcts, lacunes, cerebral microbleeds, and perivascular spaces (4). Substantial contribution to cognitive decline has been shown for frontal- and temporal-located cerebral microbleeds (60), progression of periventricular WMH (61), accumulation of lacunar infarctions (58), and perivascular spaces in combination with other markers (62).

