### Participants

Patients diagnosed with cSVD will be recruited among in-hospital patients (1st and 2nd Department of Neurology, University Clinic 3, Sechenov First Moscow State Medical University, Moscow). According to the Standards for Reporting Vascular Changes on Neuroimaging released in 2013, the neuroimaging characteristics of cSVD consist of WMH, recent small subcortical infarct, cerebral microbleeds, perivascular space, lacune of presumed vascular origin, and brain atrophy (4). The brain MRI of the patient will be assessed by trained radiologist.

Potential participants will be screened for eligibility criteria.

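### The total cSVD score is described as a sum over the disease's MRI markers, but its four items count perivascular spaces twice and white matter hyperintensities not at all

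*Protocol article*

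**What the plan says.** The Neuroimaging section states: "Calculating the total SVD score (range 0–4) will be made by adding up of scores for each cSVD marker". It then lists the items. The first two are "1 point for presence of any lacunes, 1 point for one or more cerebral microbleeds". The third and fourth are "1 point for presence of enlarged perivascular spaces (PVS) in the basal ganglia, and 1 point for presence of moderate to severe PVS"; in full, the fourth reads "1 point for presence of moderate to severe PVS in other regions". No item refers to WMH.

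The protocol lists the MRI markers of cSVD twice. At the end of the Introduction's pathophysiology section it says of the MRI features: "They consist of WMH, recent small subcortical infarcts, lacunes, cerebral microbleeds, and perivascular spaces". The Participants section says: "the neuroimaging characteristics of cSVD consist of WMH, recent small subcortical infarct, cerebral microbleeds, perivascular space", and goes on to lacunes and brain atrophy. Both lists put WMH first and name perivascular spaces once.

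The score is used in two places. Table 1 lists the cSVD Scale (0–4) at baseline and its percentage change at two years. The Statistical Analysis section takes change from baseline for the MRI scales and names the total SVD sum score among the variables to be correlated with PLMI by Spearman's method. The Outcomes section does not mention the score.

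**The concern.** The description and the item list do not agree. A sum over markers should give each scored marker its own point. Here one marker supplies half of the maximum, and the marker on which the study is built supplies nothing. WMH volume change is the primary outcome, and the Discussion treats WMH increase as a key feature of progression.

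This is a complete, affirmative scoring rule that a rater could apply as it stands, not a detail left open. One rater scores all scans, so a wrong rule would be applied uniformly, at both visits. The result would be an index weighted towards PVS, reported as total cSVD burden. A null or positive correlation with PLMI would then be read as a statement about overall burden that the score cannot support.

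**Working it through.** **Stated range.** Four items at one point each give 4 × 1 = 4, so the range 0–4 in the Neuroimaging section and Table 1 is reproduced. The neighbouring scales also add up: Fazekas 3 + 3 = 6; Scheltens 13 × 6 + 3 × 2 = 84; Rotterdam 3 + 4 = 7 regions, hence −7 to +7. The problem lies in the content of the score, and a range check would not find it.

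**Items mapped to markers.**

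| Marker (Introduction list) | Points available as written |
|---|---|
| WMH | 0 |
| Recent small subcortical infarct | 0 |
| Lacunes | 1 |
| Microbleeds | 1 |
| Perivascular spaces | 2 (basal ganglia; other regions) |
| Total | 4 |

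Four points therefore cover three distinct markers, and three of the five markers in that list are scored. PVS supplies 2/4 = half of the maximum.

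**Consequences for a single patient, as written.**
- Severe WMH and no other scored marker: 0.
- PVS in both locations and nothing else: 2.
- WMH progression between visits, other markers unchanged: change in score 0.

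**What a different fourth item would do (illustration only).** Let P be 1 if the point for PVS in other regions is earned, and W be 1 if a WMH item would be met at some cut-off. Replacing P by W changes the total by W − P.

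| P | W | Change in total |
|---|---|---|
| 0 | 0 | 0 |
| 1 | 1 | 0 |
| 1 | 0 | −1 |
| 0 | 1 | +1 |

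The range stays 0–4, now with four distinct markers. A total moves by at most one point, and only where the two items disagree. The documents give no figure for how often that happens, so the affected share of patients could lie anywhere from none to all.

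**The case against.** The strongest reply is that this is a drafting slip in a condensed article that cites a published instrument. The rater may work from the instrument rather than from the article's sentence. The marker lists also do not settle what the fourth item should be: recent small subcortical infarct, and brain atrophy in the Participants list, receive no point either, so omission alone proves nothing. The score is not a listed outcome, and WMH is measured by total and regional volume and by the Fazekas, Scheltens and Rotterdam scales. WMH volume, Fazekas and Scheltens are each correlated with PLMI separately.

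Most of this stands as a limit on size and remedy. It does not remove the contradiction. The article sets out a full scoring rule, and nothing elsewhere corrects it. What marks it as inconsistent is the combination of a second PVS point and no WMH point under a description that says "will be made by adding up of scores for each cSVD marker".

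Several stronger readings are tempting but unsupported:
- That a quarter of the scale is wrong for every patient. One item of four is in question, but totals differ only where the two items disagree.
- That every patient with WMH alone scores 0 where 1 is due. This assumes a WMH item and a cut-off that the documents do not state; below such a cut-off the score would still be 0.
- That the missing item is what makes percent change undefined. A baseline of 0 does so under any item list.
- That the planned reproduction of the earlier cross-sectional study fails. The stated aim of reproduction introduces the group comparisons, not the Spearman analysis, and whether that study used this score cannot be checked here.

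**Conclusion.** The point holds as an internal contradiction in a scoring rule that will be applied and analysed. As written, the score gives lacunes 1, microbleeds 1, PVS 2 and WMH 0, and WMH can never move it. The Spearman analysis of this score with PLMI and its change from baseline therefore would not measure total cSVD burden as the protocol itself defines the markers.

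The impact is limited to this scale. A reader might infer that the primary result is compromised; it is not, since neither the primary outcome nor any listed secondary outcome uses the score, and no conclusion about WMH depends on it.

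The conclusion rests on the protocol's text alone. That the fourth item was meant to be WMH is plausible but remains an assumption, because the cited score is not at hand. It should be corrected before rating because doing so is nearly free.

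**What to change.** Before rating starts, reconcile the item list in the Neuroimaging section with the cited score and with the marker lists in the Introduction and Participants sections. Then take one of two routes:

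1. If the fourth item was meant to be WMH, count PVS once and derive the WMH point from the Fazekas grades, at the cut-off that the cited score uses, and state that cut-off. Re-score any scans already rated.
2. If the second PVS item is intended, give the reason and stop describing the score as total cSVD burden summed over each marker.

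The cost is about one sentence in the protocol and the rating instructions. Under the first route no new imaging or reading is needed for the WMH point, because the Fazekas scale is already rated at both visits.

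Neither route deals with percent change from a baseline score of 0, which needs its own rule.

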### Outcomes

The primary outcome variable is total WMH volume change in percentage from baseline. The minimal clinically important change would be calculated based on baseline standard deviation as it was suggested by Lemieux et al. (103): the smallest effect size will be calculated by multiplying the baseline standard deviation by 0.2.

The secondary outcomes are the WMH volume change in each area of interests (periventricular, juxtacortical, infratentorial, and deep white matter), change in cognitive performance (results of each test will be processed separately) in percentage from baseline, cerebral infarct incidence, non-traumatic intracranial hemorrhage incidence, transient ischemic attack incidence, and rate of mortality due to stroke.

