**Figure 1 F1:**
[figure not shown]
Design of the study.

**Table 1 T1:** Examination protocol.

**Methods**	**Baseline**	**2-years follow-up**	**Unit of measurement**	**Range**
Polysomnography	TST	None	Min	Not defined
	SOL	None	Min	Not defined
	WASO	None	Min	Not defined
	SE	None	%	0–100
	AHI	None	Number per hour	Not defined
	LMs	None	Number during the sleep	Not defined
	LMI	None	Number per hour	Not defined
	PLMI	None	Number per hour	Not defined
	PI	None	None	0–1
	SILMS index	None	Number per hour	Not defined
	PLMWI	None	Number per hour	Not defined
	PLMAI	None	Number per hour	Not defined
Questionnaires	AUDIT	None	Points	0–40
	PSQI	None	Points	0–21
	ESS	None	Points	4–24
	GDS	None	Points	0–30
	EQ-VAS	None	Points	0–100
	ISI	None	Points	0–28
Cognitive assessment	MoCA score	MoCA score, percentage change	Points, %	0–30
	12 word test total score	12 word test total score, percentage change	Points, %	0–24
	BVRT score	BVRT score, percentage change	Points, %	0–10
	FAB score	FAB score, percentage change	Points, %	0–18
	TMT-A time	TMT-A time, percentage change	sec, %	Not defined
	TMT-B time	TMT-B time, percentage change	sec, %	Not defined
	B/A ratio	B/A ratio, percentage change	None, %	Not defined
	SDMT score	SDMT score, percentage change	points, %	not defined
	PVFT	PVFT, percentage change	Words, %	Not defined
	SVFT	SVFT, percentage change	Words, %	Not defined
Brain MRI	WMH volume	WMH volume, percentage change	ml, %	Not defined
	Fazekas Scale	Fazekas Scale, percentage change	points, %	0–6
	Scheltens Scale	Scheltens Scale, percentage change	points, %	0–84
	cSVD Scale	cSVD Scale, percentage change	points, %	0–4
	None	Rotterdam progression scale	Points	From −7 to +7

*BVRT, Benton Visual Retention Test; B/A ratio, TMT B time divided to TMT A time; PVFT, Phonemic Verbal Fluency Test; SVFT, Semantic Verbal Fluency Test*.

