### Statistical Analysis and Sample Size Calculation

The baseline values of MRI scale scores and cognitive tests (listed in Table 1) will be subtracted from the corresponding follow-up values, and percent change from baseline will be calculated. Based on the PLMI (≥15/h or <15/h), two groups will be formed. In order to reproduce results of the cross-sectional study conducted by Kang et al. (51), group comparisons will be made using the Mann–Whitney test for non-parametric statistics or unpaired *t*-test, depending on whether the distribution is normal. To assess the association between the PLMI and total cerebral SVD sum score, as well as WMH volume, Fazekas Scale score, and Scheltens Scale separately, Spearman correlation analysis will be applied. To confirm the data obtained by Leng et al. (54) and complement it with a more detailed cognitive assessment, logistic regression will be utilized to study the association between PLMS and clinically significant changes in cognition from the baseline to the follow-up visit.

Multiple regression analysis will be used to estimate the capability of each of the characteristics of PLMS (LMs, LMI, PLMI, PI, and SILMS index) to predict each of the outcome variables (except for stroke incidence and mortality rate). Adjustment for main predictors of cardiovascular risk (age, hypertension level, body mass index, diabetes mellitus, ischemic heart disease, cholesterol level, and smoking) will be made to determine if the associations are independent of these factors. Comparison of stroke incidence (separately for cerebral infarct, non-traumatic intracranial hemorrhage, and transient ischemic attack) as well as mortality rate due to stroke between two groups will be made using Pearson's chi-square test.

Spearman correlation test will be applied to evaluate the association between the PLMI and scores of self-reported questionnaires (listed in Table 1) and assess the influence of PLMS on sleep quality, mood, and daytime functioning. The level of statistical significance will be set at *p* < 0.05. All statistical analyses will be performed using SPSS version 21.0 (SPSS Inc., Chicago, IL, USA).

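### Percent change from baseline is a poor analysis scale for the primary, cognitive and visual-scale measures, and the minimal important change is set in a different unit

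*Protocol article*

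**What the plan says.** The Outcomes section fixes the primary scale: "The primary outcome variable is total WMH volume change in percentage from baseline". The Neuroimaging section defines it with baseline as the denominator: "proportional volume change will be calculated by dividing the absolute WMH volume change by baseline WMH volume with a percentage display of results". Absolute change in ml is derived first: "Baseline volumes will be subtracted from follow-up volumes to obtain absolute WMH volume change".

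Cognitive change is a secondary outcome, also in percent and test by test. For the MRI scales and cognitive tests, the Statistical Analysis section subtracts baseline from follow-up and adds that "percent change from baseline will be calculated". Table 1 lists the same form for the Fazekas, Scheltens and cSVD scales, for example "cSVD Scale, percentage change".

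The regional outcomes are less clear: "The secondary outcomes are the WMH volume change in each area of interests" does not say whether the change is absolute or relative.

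Directly after the primary outcome, the Outcomes section defines the minimal clinically important change: "the smallest effect size will be calculated by multiplying the baseline standard deviation by 0.2". The Discussion adds that the baseline level will enter the multiple regression.

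**The concern.** Three things are at stake.

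- **Primary outcome.** A percentage with a measured baseline in the denominator has large variance when that baseline is small. The multiple linear regression on which the study is sized would carry that variance.
- **Scales that can be 0.** A percentage does not exist at a zero baseline, and it gives different values to the same step elsewhere on the scale.
- **Minimal important change.** Percent change has no baseline value, so a baseline SD can only be that of the raw measure: ml, points or seconds. The threshold and the outcome it accompanies are in different units. The analysis section also plans a logistic regression on clinically significant cognitive change, and this threshold is the only criterion of that kind in the article.

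**Working it through.** The article gives no numerical value for the minimal important change and no WMH mean or SD, so there is no stated figure to reproduce. All volumes below are assumptions for illustration.

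**1. The formula at zero and small baselines.** Percent change = 100 × (follow-up − baseline) / baseline.

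- The Neuroimaging section gives the cSVD score a range of 0–4, with one point each for lacunes, microbleeds, enlarged perivascular spaces in the basal ganglia, and perivascular spaces elsewhere. WMH earns no point. A patient with WMH and none of these markers scores 0, and a first lacune (0 to 1) gives 100 × 1/0, which is undefined.
- One further marker gives 100 × 1/1 = 100% from 1, 100 × 1/2 = 50% from 2 and 100 × 1/3 = 33% from 3.
- A 1 ml increase in WMH is 200% at a baseline of 0.5 ml, 100% at 1 ml, 10% at 10 ml and 2.5% at 40 ml.

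**2. Units of the minimal important change.** Expressed as a percentage of a patient's own baseline, the threshold is 100 × 0.2 × SD / baseline.

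| Assumed SD | 0.2 × SD | at 3 ml | at 10 ml | at 30 ml |
|---|---|---|---|---|
| 8 ml | 1.6 ml | 53% | 16% | 5% |
| 12 ml | 2.4 ml | 80% | 24% | 8% |
| 15 ml | 3.0 ml | 100% | 30% | 10% |

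With a lognormal baseline of mean 10 ml and coefficient of variation (CV) 1.0, the SD is 10 ml and the threshold 2 ml. That is 111% of baseline at the 5th percentile (1.80 ml) and 7% at the 95th (27.81 ml). No single percent threshold corresponds to it.

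**3. Power on the primary outcome, relative effect.** Assumed: N = 98, 34% exposed, lognormal baseline with median 8 ml and log-SD 0.9, progression 16% faster in the exposed group, 2000 runs per scenario. Ordinary least squares on percent change with baseline as covariate is compared with log follow-up on log baseline.

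| Measurement SD | Percent change | Log follow-up on log baseline |
|---|---|---|
| 0.2 ml | 0.73 | 0.74 |
| 0.5 ml | 0.55 | 0.59 |
| 1 ml | 0.23 | 0.35 |

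With the residual log-SD varied from 0.20 to 0.28, the ranges are 0.62–0.89 against 0.63–0.90 at 0.2 ml, 0.50–0.63 against 0.54–0.72 at 0.5 ml, and 0.21–0.24 against 0.32–0.39 at 1 ml.

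**4. Power on the primary outcome, additive effect.** Assumed: 49 per group, mean baseline 10 ml, group effect 1.2 ml, SD of change 2 ml, 4000 runs, no covariates. The t-test on absolute change has about 84% power. On percent change, at baseline CV 0.5, 1.0 and 1.5, the t-test has 63%, 34% and 19%, and Mann–Whitney has 69%, 55% and 49%.

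**The case against.** The strongest reply is that the protocol is less exposed than the points above suggest.

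- **Not every change measure is a percentage.** The Rotterdam scale is in points from −7 to +7, absolute WMH change is also derived, and the regional wording is open. This stands, so the point is limited to the measures named in the heading.
- **A reader might see a contradiction** between Table 1 and the Neuroimaging statement "Change scores will be obtained by subtracting the baseline scores from the follow-up scores". There is none: the analysis section subtracts first and then computes the percentage, so the subtraction can be read as its numerator.
- **A reader might infer that patients are selectively lost from the primary outcome.** The documents do not support this. Entry requires cSVD diagnosed on MRI and clinical features, so a total WMH volume of exactly 0 should be uncommon. The zero problem concerns the visual scales, and regional volumes if taken as percent. The visual scales are not named as primary or secondary outcomes, though the analysis section does convert them to percent change.
- **Mann–Whitney is planned when the distribution is not normal.** Percent change is a monotone function of the follow-up to baseline ratio, so extreme percentages cannot dominate a rank test by their size. This stands for the group comparison. The regression has no such fallback.
- **Baseline enters the regression.** That helps with baseline imbalance, but it does not repair a zero or noisy denominator.
- **The threshold could be applied to the absolute changes.** It could, but the protocol does not say so, and it places the threshold beside a percent outcome.
- **The power figures rest on assumptions.** They do. The relative-effect model suits the log analysis and the additive model suits absolute change; the protocol establishes neither.

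**Conclusion.** The point holds for the primary outcome, the cognitive tests and the Fazekas, Scheltens and cSVD scales. Two parts follow from the protocol's own definitions and need no assumption. Percent change is undefined at a baseline of 0 and gives unequal values to equal steps on the short scales. The minimal important change is in raw units, so it cannot be applied to a percent outcome as stated.

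The third part, loss of power in the primary regression, depends on conditions. Under a relative effect it is about one percentage point if volumes are measured to within 0.2 ml and about 12 points (0.35 − 0.23) at 1 ml. Under an additive effect, without covariates, it is larger. The article gives neither the measurement error nor the baseline distribution, so it cannot be called large with confidence.

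It would go too far to say that the primary comparison is driven by the patients with the least disease, because the rank test is not dominated in that way.

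**What to change.** 1. **Primary analysis:** log(follow-up total WMH volume) regressed on PLMS group, with log(baseline volume) as covariate alongside the planned adjustments. Report the back-transformed ratio, which still reads as a relative change. State a rule for the rare zero volume, because the log also fails there.
2. **Regional volumes, visual scales and cognitive tests:** analyse the follow-up value or the absolute change, adjusted for baseline, and say which applies to the regional volumes.
3. **Minimal important change:** state it on the scale that is analysed, as a ratio for total WMH volume and in raw units for the other measures, including the criterion for clinically significant cognitive change.
4. **Percent change:** keep it as a descriptive table only.

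The cost is rewording of the outcomes and analysis text before the data are analysed; no new data are collected. The downside is that results appear as ratios or points instead of raw percentages.
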